#### 2.1.1 Sample size

As this study is a randomized controlled trial, the respondents will be divided into manual intervention group, artificial intelligence (AI) intervention group, artificial intelligence and manual combined intervention group, and observe the BMI of pregnant women, maternal weight and maternal adverse pregnancy outcomes as the main outcome indicators. The sample size was calculated based on an expected effect size of 0.5, which corresponds to the minimal clinically important difference (MCID) of the primary outcome. This MCID was determined based on previous literature and clinical judgment. Setting bilateral α = 0.05, the degree of certainty was 90%. Using the PASS15 software, we obtained a sample size of N1 = 40 cases for the group and N2 = 40 cases for the group and N3 = 40 cases for the group. For a total of at least 120 subjects to be included in the study.

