### 2.4 Outcomes

#### 2.4.1 Primary outcomes

The primary outcomes of the study include maternal body mass index (BMI), maternal weight, and adverse pregnancy outcomes. The primary outcome measures (such as BMI, maternal weight, and adverse pregnancy outcomes) will be assessed using Repeated Measures ANOVA or Mixed Effects Models to evaluate the intervention effects. For long-term effect analysis, Generalized Estimating Equations (GEE) or Cox Proportional Hazards Models will be employed to assess the short-term, medium-term, and long-term impacts of the interventions. Cost-effectiveness analysis will be conducted using Quality-Adjusted Life Years (QALY) and Incremental Cost-Effectiveness Ratios (ICER) to evaluate the economic efficiency of different intervention measures, with sensitivity analysis performed to verify the robustness of the results.

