#### 2.4.2 Secondary outcomes

The secondary outcomes encompass physiological indicators such as blood pressure and blood lipid profiles (including triglycerides, low-density lipoprotein (LDL), high-density lipoprotein (HDL), and very-low-density lipoprotein (VLDL) cholesterol levels), quality of life assessments, mental health evaluations, and lifestyle factors (dietary habits and physical exercise patterns). Secondary outcome measures (such as blood pressure, lipid levels, and quality of life) will be analyzed using multiple linear regression or logistic regression, controlling for confounding factors such as age and baseline BMI, to assess the independent effects of the interventions. Subgroup analysis will further explore the differences in intervention effects across subgroups defined by factors such as age and BMI classification, with interaction tests conducted to verify the robustness of the results.

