Social and demographic factors	Family related factors	Survey	Parents' medical history of hypertension, diabetes, and cardiovascular disease, annual family income	√					
Health status		Survey and Medical record	Height, weight, BMI, blood pressure and blood sugar, smoking and drinking status, WHO−5	√	√	√	√	√	√
Activity	Physical activities	Survey	Physical Activity Rating Scale-3, PARS-3	√	√	√	√	√	√
Psychosocial status	Quality of life	Survey	EQ-5D version, EQ-5D-5L	√	√	√	√	√	√
	Sleep	Survey	Pittsburgh sleep quality index, PSQI	√	√	√	√	√	√
	Social support	Survey	Social support rate scale, PSSS-SF	√	√	√	√	√	√
Psychology status	Anxiety	Survey	General Anxiety Disorder-7, GAD-7	√	√	√	√	√	√
	Stress	Survey	Perceived Stress Scale, PSS-4	√	√	√	√	√	√
	Self-efficacy	Survey	General Self-Efficacy Scale	√	√	√	√	√	√
	Family health	Survey	The Family Health Scale short-form, FHS-SF	√	√	√	√	√	√
Cost-effectiveness	Tracking cost	Survey and medical record		√	√	√	√	√	√
Qualitative results			Effect of trial	√	√	√	√	√	√

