### 2.6 Statistical analysis

Participants' socio-demographics are presented as count and proportion, and the χ^2^ test was used to assess categorical variables. The continuous variables normally distributed were assessed by the student's *t*-test. The Fisher's exact or the chi-square test was adopted for categorical data, and statistical significance was set at *p* < 0.05. The main analysis was performed using generalized estimating equations (GEE) model. The GEE solved the problem of correlation of longitudinal data, utilizing the results of each measurement in the longitudinal data, which greatly reduces the loss of information (20). To clarify whether socioeconomic status affects the effectiveness of ILSM, we conducted several subgroup analyses for physiological health outcomes and health behaviors, and added the interaction terms to generalized estimating equations model to assess the interactions between time (at baseline, 3-month, 6-month, and 18-month) and group (intervention and control). We also used GEE to analyze the health benefits of intervention and control groups among participants with different socioeconomic status. Significance level of the associations in the final model was set at *P*-value 0.05. The data were analyzed using SPSS 20.0 (IBM Corporation, Armonk, NY, USA).

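### The primary BMI and weight models fix neither the role of the baseline value nor the primary contrast, so precision may be lost, depending on the contrast tested

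*Protocol article*

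**What the plan says.** Section 2.4.1 gives BMI, weight and adverse pregnancy outcomes one set of methods: "The primary outcome measures (such as BMI, maternal weight, and adverse pregnancy outcomes) will be assessed using Repeated Measures ANOVA or Mixed Effects Models". It adds GEE or Cox models for effects over time. Section 2.6 says "The main analysis was performed using generalized estimating equations (GEE) model". Neither section names a covariate for the primary models, and neither says whether the primary test is a group main effect, a group-by-time interaction or a comparison at one visit.

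Section 2.4.2 does state an adjustment, for the secondary outcomes: "controlling for confounding factors such as age and baseline BMI, to assess the independent effects of the interventions".

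The baseline values are available. The health-status row of Table 1 (section 2.5) includes "Height, weight, BMI, blood pressure and blood sugar" and is ticked at T-0 and at every later time point. Section 2.2 describes simple randomisation, and the limitations in section 3 acknowledge that the groups are not balanced by stratification.

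**The concern.** Baseline BMI is named as a covariate for blood pressure, lipids and quality of life, but not for follow-up BMI, where it is the outcome's own starting value and should predict best. The design does not balance it either.

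If the primary test ignores the T-0 value, stable differences between women stay in the error term, and a chance difference in starting weight carries through to the estimated effect. If the test is a simple change from baseline, stable differences cancel, but the change over-corrects when r is below 1. Adjusting for the T-0 value avoids both problems. At stake is the precision of a trial with only 40 women per arm.

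**Working it through.** **Inputs from section 2.1.1.** "The sample size was calculated based on an expected effect size of 0.5"; "Setting bilateral α = 0.05, the degree of certainty was 90" per cent; 40 per arm in three arms; "For a total of at least 120 subjects to be included in the study". The type of effect size, the outcome it refers to, the SD and the baseline correlation are not given. I read 0.5 as a standardised mean difference d on the follow-up SD, and show r as a range.

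**The plan's own figure.** For two arms, n = 2(1.960 + 1.282)²/0.5² = 84.06, so 85 per arm, not 40. The other standard readings tried (one-sided test, 80% power, one-way ANOVA with f = 0.5 or 0.25) do not give 40 either. With d = 0.5, 40 per arm would need an unstated r of about 0.72 with baseline adjustment (√(1 − 40/84.06)) or 0.76 with change scores (1 − 40/(2 × 84.06)). The sample size is a separate matter, but it shows how much the handling of baseline can matter here.

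**Power for one pairwise comparison** (noncentral t, 40 per arm, two-sided 0.05, noncentrality = effect × √(40/2)):

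- Follow-up visit only: effect = 0.5 at any r; noncentrality 2.236; power 59.8%.
- Change from baseline: effect = 0.5/√(2(1 − r)).
- Baseline-adjusted: effect = 0.5/√(1 − r²), with one degree of freedom fewer.
- Group main effect over five visits (baseline plus the four follow-ups in section 2.1), with compound symmetry and a constant effect of 0.5 after baseline: the mean effect is 0.5 × 4/5 = 0.4 and the variance is (1 + 4r)/5, so effect = 0.4/√((1 + 4r)/5).

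Example at r = 0.7: change 0.5/√0.6 = 0.645; adjusted 0.5/√0.51 = 0.700; main effect 0.4/√0.76 = 0.459.

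| r | Follow-up only | Change | Adjusted | Main effect, 5 visits |
|---|---|---|---|---|
| 0.3 | 59.8% | 46.3% | 63.9% | 75.9% |
| 0.5 | 59.8% | 59.8% | 72.2% | 62.6% |
| 0.7 | 59.8% | 81.4% | 87.1% | 52.7% |
| 0.8 | 59.8% | 93.7% | 95.7% | 48.7% |
| 0.9 | 59.8% | 99.9% | 99.9% | 45.3% |

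The first three power columns use one follow-up visit. The last averages several visits, which helps it at low r, so it is not like for like. Its power falls as r rises because averaging removes less variance, while the baseline visit, which carries no effect, still dilutes the difference.

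**Chance imbalance.** The difference in baseline means between two arms has standard error √(2/40) = 0.224 SD. By simulation, some pair of the three arms differs by more than 0.25 SD with probability 0.50, and by more than 0.30 SD with probability 0.37. Given a 0.3 SD difference, the expected shift in the realised estimate is:

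- follow-up only, 0.3r: 0.21 SD at r = 0.7, 0.27 SD at r = 0.9;
- change, 0.3(r − 1): −0.09 SD at r = 0.7, −0.03 SD at r = 0.9;
- baseline-adjusted: 0.

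**The case against.** The strongest reply is that silence is not a decision against adjustment. An article condenses its protocol, and a covariate list is commonly left to an analysis plan. That stands as far as it goes: a reader might infer that the primary models will definitely be unadjusted, but the text does not say so. What remains is that the article does state an adjustment and ties it to the secondary outcomes only, while leaving the primary contrast open.

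A second reply is that a repeated-measures model can use baseline as one of the visits. Section 2.6 does list baseline as a level of time in a time-by-group interaction. Under that contrast stable between-woman variance cancels and little is lost. High r is plausible for weight and BMI, though this is an assumption, and at r of 0.7 or more the difference from adjustment is small. This also stands, so a reader who infers that power is certainly lost goes beyond the documents. But the sentence belongs to the socioeconomic subgroup analyses. It refers to two groups and to 3, 6 and 18 months, which match neither the three arms nor the visits in section 2.1. It cannot be taken as the primary specification.

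Third, a reader might infer that chance imbalance biases the comparison. It does not: under randomisation the type I error already allows for it. It costs precision and distorts the estimate actually obtained.

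Finally, adverse pregnancy outcomes have no baseline value, so none of the power figures apply to them.

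**Conclusion.** The point holds in conditional form. The primary BMI and weight analysis leaves the contrast and the role of the T-0 value open, and the article is inconsistent in adjusting the secondary models for baseline BMI but not, as described, the primary ones.

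For r of 0.7 to 0.9, adjusting gains 27 to 40 points of pairwise power over a follow-up-only test. It gains more against a main effect that averages in the baseline visit. Against a group-by-time change contrast it gains about 6 points at r = 0.7, 2 at r = 0.8 and almost none at r = 0.9. Over the range shown, adjustment is never worse than the follow-up-only or change analysis of the same visit.

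These sizes rest on reading 0.5 as a standardised mean difference, on one follow-up visit (except for the main-effect column) and on an assumed r. They do not show that the trial will lose power, only that readings the text allows would.

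**What to change.** In sections 2.4.1 and 2.6, state one primary longitudinal model for BMI and for weight (a mixed model or GEE, not a choice among several). It should use the post-baseline visits, with arm, visit, arm by visit, and the woman's own T-0 value and its interaction with visit as covariates. A constrained-baseline model would serve equally well. Name the primary contrast: which arms, and at which visit or averaged over which visits.

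Optionally, adjust adverse pregnancy outcomes for baseline BMI and age as prognostic covariates, in line with section 2.4.2; no gain is quantified for them.

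The cost is a sentence or two in each section. The T-0 values are already collected, so no new data are needed.

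### Repeated-measures methods are assigned to adverse outcomes that occur at most once, and sections 2.4.1, 2.4.2 and 2.6 name conflicting models for the repeated outcomes

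*Protocol article*

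**What the plan says.** Section 2.4.1 of the protocol article sets three primary outcomes: "The primary outcomes of the study include maternal body mass index (BMI), maternal weight, and adverse pregnancy outcomes". It assigns one pair of methods to all of them and lists the adverse outcomes by name: "such as BMI, maternal weight, and adverse pregnancy outcomes) will be assessed using Repeated Measures ANOVA or Mixed Effects Models". It then adds: "For long-term effect analysis, Generalized Estimating Equations (GEE) or Cox Proportional Hazards Models will be employed". That sentence goes on to cover short- and medium-term effects as well, and it ties neither method to a particular outcome.

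Section 2.4.2 says that secondary outcomes, with blood pressure, lipids and quality of life as examples, "will be analyzed using multiple linear regression or logistic regression, controlling for confounding factors such as age and baseline BMI". It names no visit.

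Section 2.6 states: "The main analysis was performed using generalized estimating equations (GEE) model". Its reason is that GEE handles the correlation of longitudinal data. It also uses GEE, with interaction terms, in subgroup analyses of physiological outcomes and health behaviours. Those terms refer to two groups and to baseline, 3, 6 and 18 months. The same section names Fisher's exact and chi-square tests for categorical data without saying which outcomes they serve.

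Table 1 in section 2.5 ticks "Height, weight, BMI, blood pressure and blood sugar" and "EQ-5D version, EQ-5D-5L" at all six occasions, T-0 to T-5. It has no row for adverse pregnancy outcomes.

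**The concern.** There are three separate problems.

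- A primary outcome is paired with a method that needs repeated measurements, although its nature gives one result per woman.
- Two sections give different answers to the question of which model yields the main result for BMI and weight. Section 2.4.1 also leaves its own choice open with an unresolved alternative.
- Secondary outcomes recorded at every visit are assigned a single-record regression with no visit chosen, while another section argues for a longitudinal method for the same kind of data.

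The stake is that the model behind the main result could be picked after the data are seen. The candidates also treat missed visits differently, so they need not analyse the same women. An analysis plan can add detail to a protocol statement, but it cannot elaborate two statements that disagree; one of them has to be corrected.

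**Working it through.** The protocol article gives no figure on this point to reproduce. Its 40 women per arm (section 2.1.1) enters only as a multiplier in step 4, and how that number was obtained is a separate matter. The check is mainly a comparison of sections.

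| Outcome | How it is recorded | Sections 2.4.1 and 2.4.2 | Section 2.6 |
|---|---|---|---|
| BMI, weight | T-0 to T-5 | Repeated-measures ANOVA or mixed model; GEE or Cox for long-term effects | GEE as main analysis |
| Adverse pregnancy outcomes | No row in Table 1 | Repeated-measures ANOVA or mixed model | Not addressed by name; GEE and chi-square/Fisher both present |
| Blood pressure | T-0 to T-5 | Linear or logistic regression, no visit | GEE for physiological outcomes (subgroup and interaction analyses) |
| Quality of life | T-0 to T-5 | Linear or logistic regression, no visit | Not named, but the reason given for GEE applies |

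**Step 1, adverse outcomes.** The Introduction's maternal examples include preeclampsia, caesarean delivery and gestational diabetes. Each is present or absent, and each occurs at most once in a pregnancy. Repeated-measures ANOVA needs a continuous response measured several times in the same woman, and here there is none. The alternative in the same sentence does not help: even a logistic mixed model has no within-woman repeats to use when there is one record per woman.

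**Step 2, BMI and weight.** Three methods could produce the main result: repeated-measures ANOVA, a mixed model (both from section 2.4.1) and GEE (section 2.6). Section 2.4.1 places GEE under long-term effects, whereas section 2.6 makes it the main analysis. The group and time terms of section 2.6 do not match the design either. The trial has three arms, not two. Section 2.1 schedules baseline at about 12 weeks, then visits at about 20, 28 and 36 weeks and at 3 months postpartum.

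**Step 3, secondary outcomes.** Regression on one record per woman is sound at a single chosen visit, but none is chosen. For blood pressure, section 2.4.2 and section 2.6 point to different methods.

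**Step 4, illustration of how the choice matters.** Standard repeated-measures ANOVA uses only women with every visit. If a proportion p misses each of k follow-ups independently, the share kept is (1 − p)^k. The article gives no p, so p = 0.10 is assumed.

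- k = 4 (section 2.1): 0.9^4 = 0.656, and 0.656 × 40 = 26.2, about 26 women per arm.
- k = 5 (T-1 to T-5 in Table 1): 0.9^5 = 0.590, and 0.590 × 40 = 23.6, about 24 women per arm.

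A mixed model or GEE would keep the observed visits of the remaining women.

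**The case against.** The strongest reply is that the article does contain usable methods. Section 2.6 mentions chi-square and Fisher tests for categorical data, and GEE with a binary response and one record per woman is logistic regression with robust errors. This stands. A reader might infer that one primary outcome has no valid analysis at all; the text does not support that. The defect is that the method explicitly assigned does not fit and the usable ones are not linked to the outcome.

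The once-only nature of the adverse outcomes is inferred from the Introduction's examples, because the article gives no operational list. Some of those diagnoses arise at a particular gestational age, so a time-to-event analysis is conceivable. It follows that Cox is unanchored, not that it is wrong in principle.

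A reader might also infer that the secondary regressions will stack all visits as independent rows and so inflate the type I error. Section 2.4.2 does not propose this, so no such inflation can be charged to the plan.

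Nor does the article plan to leave out the baseline value of each outcome. Its covariates are given as examples from an open list, so baseline adjustment is a recommendation and not an error found.

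Finally, the loss of women in step 4 arises only if repeated-measures ANOVA is chosen over the alternatives, and only under the assumed missingness.

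**Conclusion.** The point holds as an assigned method that does not fit and as a contradiction between sections. It is wrong as written, and it is not detail that a protocol article may leave to another document.

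Three conclusions stand without any assumed number, the first resting on the Introduction's examples:

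- Repeated-measures ANOVA or a mixed model does not fit adverse pregnancy outcomes.
- Sections 2.4.1 and 2.6 name different main models for BMI and weight.
- Section 2.4.2 names no visit for outcomes collected at every time point, and it disagrees with section 2.6 on physiological outcomes.

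The effect on the trial's result cannot be sized from the article. The 66% retention (59% with five follow-ups) shows only why the choice is not neutral; it rests on an assumed 10% missed at each follow-up, independently.

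**What to change.** - **Weight, BMI and the repeated secondary outcomes:** name one longitudinal model, either a mixed model or GEE. Include the three arms, the actual visits of section 2.1 (with the six occasions of Table 1 reconciled to them), arm by visit, and the baseline value of the outcome as covariate. State one visit for the primary contrast.
- **Adverse pregnancy outcomes:** use one record per woman and one binary model, for example modified Poisson or logistic regression. State which events count, or refer to where the full protocol lists them.
- **Repeated-measures ANOVA:** remove it, since it drops women with a missed visit.
- **Cox model:** keep it only if a time-to-event outcome is defined, with its time origin and censoring rule.
- **Consistency:** make sections 2.4.1, 2.4.2 and 2.6 agree, and replace the two-group, 0/3/6/18-month terms in section 2.6.

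The cost is wording. No extra visit or participant is needed for the modelling changes, and the methods are available in the stated software. The one item beyond the choice of model is the list of adverse events, if it is not already written elsewhere.

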**Results:**

The study will evaluate the effects of health interventions on obese pregnant women through primary outcomes (e.g., BMI, weight, adverse pregnancy outcomes) and secondary outcomes (e.g., physiological indicators, quality of life, mental health) using various statistical methods. The results will provide insights into the intervention's effectiveness and cost-effectiveness across different socioeconomic groups.

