In China, patients with obesity and chronic diseases face severe challenges. Internationally, interventions for patients with obesity and chronic diseases are often supported by professional medical teams and community health programs. In contrast, Chinese patients tend to rely on hospitals and themselves. In view of China, therapeutic lifestyle intervention combined with AI technology, as an innovative intervention, is easy to implement and cost-effective. Through AI technology, personalized lifestyle advice can be provided, monitoring patient health data and timely adjusting treatment options. This intervention not only facilitates patients to receive management at home, but also can deliver professional support to meet the needs of patients in the process of lifestyle change effectively and efficiently. Therefore, research targeting this area has important practical significance and urgency.

This study designed a randomized controlled study to propose an AI-driven therapeutic lifestyle change (AI-TLC) intervention. Through personalization, continuous tracking feedback, intelligent decision aid, evaluate the influence of AI-TLC intervention on health behavior and health outcomes of obese pregnant women, determine the applicability and universality of AI-TLC intervention, provide innovative, efficient, and personalized health intervention for obese pregnant women, and provide new perspectives and methods for related scientific research and clinical practice.

Specific objectives are:

Primary: Can the intervention program driven by artificial intelligence (AI)–facilitated therapeutic lifestyle changes effectively promote improvements in health behaviors and health outcomes among pregnant women who are overweight or obese?

Sub-question 1:

Do the effects of the intervention differ among pregnant women of varying ages and degrees of obesity?

Sub-question 2: From a cost-benefit perspective, which level of intervention is the most effective (human-only vs. AI-only vs. human + AI)?

Sub-question 3: What are the short-term, medium-term, and long-term effects of this intervention program? What mechanisms need to be added to achieve better long-term outcomes?

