## 2 Methods and analysis

### 2.1 Study participants and sample size

The baseline assessment for this study will be conducted at approximately 12 weeks of gestation. Follow-up visits are scheduled at approximately 20, 28, and 36 weeks of gestation, as well as at 3 months postpartum (24–32 weeks post-delivery). Figure 1 presents the detailed flowchart of this study.

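### With 40 women per arm, ICERs alone may not reliably rank the three programmes; make net monetary benefit, adjusted for baseline utility, the decision statistic

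*Protocol article*

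**What the plan says.** The specific objectives in the Introduction pose a three-way choice: "From a cost-benefit perspective, which level of intervention is the most effective", with the options human-only, AI-only and human + AI. Section 2.1.1 confirms three active arms ("manual intervention group, artificial intelligence (AI) intervention group, artificial intelligence and manual combined intervention group") with 40 women each and no untreated control.

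Section 2.4.1 names the economic method: "Cost-effectiveness analysis will be conducted using Quality-Adjusted Life Years (QALY) and Incremental Cost-Effectiveness Ratios (ICER"), "with sensitivity analysis performed to verify the robustness of the results". It does not say what kind of sensitivity analysis is meant and gives no value per QALY. Table 1 schedules EQ-5D-5L and cost tracking at T-0 to T-5, so baseline utility is collected.

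The period over which QALYs accrue is not settled. Section 2.1 has baseline "conducted at approximately 12 weeks of gestation" and a last visit at 3 months postpartum, which the same sentence explains as 24 to 32 weeks after delivery. The limitations in section 3 say up to 3 months postpartum. Section 2.6 lists an 18-month time point. Section 2.1 describes five assessments, whereas Table 1 has six columns.

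The abstract's Results paragraph promises insight into "effectiveness and cost-effectiveness across different socioeconomic groups".

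**The concern.** An ICER is a cost difference divided by a QALY difference. Three of its properties matter here, whatever the data turn out to be:

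- A negative value can mean cheaper and better, or dearer and worse.
- When the confidence interval for the QALY difference includes zero, the Fieller confidence set for the ratio is not a bounded interval.
- Among options of which none dominates, ICERs pick a winner only once a value per QALY is set.

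All three arms deliver therapeutic lifestyle plans built on the same health data, so small utility differences between them are plausible. Randomisation is simple and unstratified (section 2.2), so chance imbalance in baseline utility passes into an unadjusted QALY comparison. At stake is the answer to one of the trial's three sub-questions. Section 3 presents it as a basis for advising policymakers.

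**Working it through.** The article states no utility difference, utility SD, cost or expected ICER, so there is no plan figure to reproduce. The check below uses assumed ranges.

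**Inputs.** From the document: n = 40 per arm. Assumed: utility SD (s) 0.10 to 0.15; equal within-woman correlation (r) 0.4 to 0.6; m = 5 equally weighted readings; true mean utility difference over the horizon (d) 0.01 to 0.05; delivery at 40 weeks.

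**1. Horizon (T) from 12 weeks of gestation.**
- 3 months postpartum: 28 + 13 = 41 weeks, 0.79 year.
- 24 to 32 weeks after delivery: 52 to 60 weeks, 1.0 to 1.15 years.
- 18 months read from baseline: 1.5 years.

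**2. Standard error of a QALY difference between two arms.** With f = (1 + (m − 1)r)/m, SE = T × s × √f × √(2/40). Here f = 0.52 at r = 0.4 and 0.68 at r = 0.6.
- Low: 0.79 × 0.10 × 0.721 × 0.2236 = 0.0127 QALY.
- High: 0.79 × 0.15 × 0.825 × 0.2236 = 0.0219 QALY.

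**3. Probability of the wrong sign.** This is Φ(−dT/SE). T multiplies both dT and SE and cancels, leaving Φ(−d/SE_u), where SE_u = s × √f × 0.2236 = 0.0161 to 0.0277.

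| True mean utility difference | Wrong sign |
|---|---|
| 0.01 | 27% to 36% |
| 0.02 | 11% to 23% |
| 0.03 | 3% to 14% |
| 0.05 | 0.1% to 3.5% |

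With six readings instead of five (f = 0.50 to 0.667), the range for 0.01 to 0.03 is still 3% to 36%.

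**4. How often the 95% interval for the QALY difference includes zero.** With z = d/SE_u, this is 1 − Φ(z − 1.96) − Φ(−z − 1.96).
- z = 0.03/0.0161 = 1.86 gives 54%.
- z = 0.01/0.0277 = 0.36 gives about 93.5%.

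In those trials the Fieller set for the ICER is unbounded.

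**5. Gain from adjusting for baseline utility.** Under the same model the T-0 reading explains a fraction f of the variance of the five-reading mean, so the SE is multiplied by √(1 − f).
- r = 0.4: √0.48 = 0.693, a cut of about 31%.
- r = 0.6: √0.32 = 0.566, a cut of about 43%.

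The wrong-sign range for d = 0.01 to 0.03 falls from 3–36% to about 0.2–28%.

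**6. Ratio against net benefit: an illustration.** Assumed mean costs are 2,000 (manual), 500 (AI) and 2,500 (combined), cost SD 3,000, value per QALY 100,000, s = 0.12 and r = 0.5, with a utility gain of 0.02 in the combined arm only. All money is in arbitrary units. At 0.79 year the simulated ICER of combined against AI has a 95% range of about −1.14 million to +1.27 million. Net benefit on the same data ranks first the manual arm in 11% of simulated trials, AI in 53% and combined in 36%. Across the simulated gains (0 to 0.04) and two horizons (0.79 and 1.15 years), the arm most often ranked first is chosen in 49% to 83%.

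**7. Why the horizon still matters.** It cancels from the sign-error rate but not from the decision. In the same illustration, with costs held fixed, true net benefit of the combined arm is 100,000 × 0.02 × 0.79 − 2,500 = −920 at 0.79 year and 100,000 × 0.02 × 1.15 − 2,500 = −200 at 1.15 years. The AI arm stands at −500 at both. The best arm changes with the horizon.

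**The case against.** QALYs and ICERs are a standard method. A condensed article may leave the value per QALY, dominance rules and bootstrap to a fuller plan, so their absence is not a fault. Section 2.4.1 fixes no single comparator, and its sensitivity analysis could be probabilistic. All of that stands. What remains is that the article names the ICER as the statistic for a three-way choice, when a better one is available on the same data.

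A reader might infer three stronger claims that the document does not support:

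- **That the QALY differences will be near zero.** No utility inputs are given, so this would be a forecast. At a difference of 0.05 the sign is nearly always right.
- **That a follow-up of well under a year causes the instability.** That length fits only one of the conflicting horizons, and the horizon cancels from the sign-error rate. The drivers are the sample size and the size of the utility difference relative to its spread.
- **That the arms cannot be ranked.** Dominance rules or net benefit on the same data do rank them, with stated uncertainty.

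It is also fair to say that net benefit does not create information: in the illustration the leading arm comes first in only 49% to 83% of trials. It removes the ambiguity of the ratio, and baseline adjustment reduces the noise. Baseline imbalance is part of the SE in step 2, not an extra error on top of it.

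On socioeconomic groups, the abstract promises only insights, section 2.6 plans such subgroups for physiological outcomes and behaviours rather than cost, and section 3 already warns about small subgroups. A descriptive label is enough.

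**Conclusion.** The point holds conditionally and is worth acting on. If true mean utility differences between the arms are 0.01 to 0.03, then with 40 per arm the QALY difference has the wrong sign in about 3% to 36% of trials. Its 95% interval includes zero in about 54% to 94%, and ICERs alone cannot then reliably rank the programmes. If the difference is 0.05, the sign is wrong in only about 0.1% to 3.5%. These figures rest on the assumed SD, correlation and equally weighted readings, none of which the article supplies. This is a recommended improvement to one sub-question and does not touch the primary outcomes. Separately, the follow-up statements contradict each other and must be reconciled, because the QALY period can change which arm is best.

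**What to change.** In section 2.4.1:

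- Make incremental net monetary benefit the decision statistic: for each woman, value per QALY times QALYs minus cost, over a stated range of values per QALY.
- Regress it on arm with T-0 EQ-5D-5L utility as a covariate.
- Bootstrap women and report, over that range, the probability that each of the three arms is best (acceptability curves).
- Show ICERs as description, between non-dominated arms only.
- Fix one QALY period by reconciling sections 2.1, 2.6 and 3, and match the assessments in section 2.1 to the columns of Table 1.
- In the abstract, label any cost-effectiveness result by socioeconomic group as descriptive.

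The cost is revised wording and a short bootstrap program; no new data are needed. The downside is that the answer to sub-question 2 becomes a probability statement that depends on the value placed on a QALY.
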